#### (1) Data distribution assessment

(a) Normality: Evaluated using the Shapiro–Wilk test (*p* ≥ 0.05 required for normality).

(b) Homogeneity of variance: Assessed via Levene's test (*p* ≥ 0.05 required for equal variances).

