#### (2) Between-group comparisons

(a) Parametric approach: For normally distributed data with homogeneous variances, one-way analysis of variance (ANOVA) is performed. If the omnibus test is significant (*p* < 0.05), *post hoc* pairwise comparisons are conducted using Tukey's HSD to control the family-wise error rate (FWER).

(b) Non-parametric approach: For non-normal or heteroscedastic data, the Kruskal–Wallis test is applied, followed by Dunn's test with Bonferroni-adjusted *p*-values (α = 0.017).

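### Pretests on the outcome data choose between a mean-based and a rank-based primary test, unequal variance alone leads to Kruskal–Wallis, and the Bonferroni wording on that branch is ambiguous

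*Protocol article*

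**What the plan says.** Under Statistical analysis plan, item (1), the protocol article sets two gates. Normality: "Evaluated using the Shapiro–Wilk test (*p* ≥ 0.05 required for normality". Equal variances: "Assessed via Levene's test (*p* ≥ 0.05 required for equal variances".

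Item (2) then branches. If both gates are passed: "For normally distributed data with homogeneous variances, one-way analysis of variance (ANOVA) is performed", and after a significant omnibus test, "pairwise comparisons are conducted using Tukey's HSD to control the family-wise error rate (FWER". If either gate fails: "For non-normal or heteroscedastic data, the Kruskal–Wallis test is applied", "followed by Dunn's test with Bonferroni-adjusted *p*-values (α = 0.017".

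Item (4)(a) adds Bonferroni-corrected pairwise t-tests at an adjusted level of 0.017 as a sensitivity analysis. They do not depend on the gates.

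The sample size section works with a difference in means: δ = 5 points, σ = 8.2, 30 per group before dropout. The two primary scales are bounded sum scores, assessed after treatment at weeks 6, 12 and 24.

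**The concern.** Three things are wrong with the rule as written.

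- **The quantity compared depends on the data.** One branch compares means and the other compares rank distributions. Nothing holds the branch constant, so CVS-FAS and QBD-SAS, or two visits of one scale, may be compared on different quantities.
- **Kruskal–Wallis is prescribed for unequal variance alone.** It tests equality of distributions. When spreads differ it is not a test of equal means, and it returns no estimate that can be set against δ = 5.
- **The pairwise threshold is ambiguous.** Bonferroni-adjusted p-values belong against 0.05; raw p-values belong against 0.05/3. The text pairs adjusted p-values with the divided level.

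At stake are the pairwise contrasts that carry the trial's conclusions: umbilical needle against traditional acupuncture, and with against without the three-needle component.

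**Working it through.** **Inputs from the protocol article.** Both gates at 0.05; three groups; 30 evaluable per group; δ = 5; σ = 8.2; pairwise level 0.017. CVS-FAS items sum to 8+4+4+4+2+4+4 = 30; QBD-SAS items to 6+6+3+3+3 = 21.

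**Assumptions.** The article gives no distribution shape and no SD other than 8.2 (with a 7.0–9.0 range). All other shapes and SDs below are assumed and shown as a range. Simulations used 3 × 30 patients and 4,000 to 6,000 runs per scenario (Monte Carlo SE about 0.003 at 0.05).

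**1. The stated threshold.** 0.05/3 = 0.0167, which is 0.017 at three decimals. It reproduces as a single Bonferroni correction for three comparisons.

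**2. How often the gate diverts well-behaved data.** Item (1) does not say whether Shapiro–Wilk is run per arm or on pooled residuals.
- Per arm (three tests plus Levene): 1 − 0.95⁴ = 18.5% if independent; simulated 18–19%.
- Pooled residuals plus Levene: 1 − 0.95² = 9.8% if independent; simulated about 11%.
- A 0–30 score with a floor effect (normal, mean 6, SD 8.2, rounded and clipped; Shapiro–Wilk per arm): more than 99%.

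**3. Omnibus type I error of the whole two-stage rule, equal means.**

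| Assumed data | Two-stage rule | Welch ANOVA |
|---|---|---|
| Normal, SD 8.2 in all arms | 0.049 | 0.049 |
| Normal, SD 5/8.2/12 | 0.045 | 0.044 |
| Normal, SD 4/4/12 | 0.062 | 0.055 |
| Exponential, equal SD | 0.045 | 0.047 |
| Bounded 0–30, floor effect | 0.051 | 0.054 |
| Gamma, mean 8, SD 4/4/5 | about 0.06–0.07 | about 0.05 |
| Gamma, mean 8, SD 4/4/6 | about 0.09 | about 0.05–0.06 |
| Gamma, mean 8, SD 4/4/8 | about 0.21 | about 0.06 |
| Shifted exponential, SD 5/8.2/12 | 0.29 | 0.066 |

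The last four rows combine skew with unequal spread, and inflation grows with the imbalance. In the last row ordinary ANOVA rejects in 0.061 of runs, so the gate sends the data to the test that is further from nominal for a comparison of means.

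**4. The double correction, if read literally.** Adjusted p compared with 0.05/3 means raw p compared with 0.05/9 = 0.0056.
- Family-wise error of Kruskal–Wallis plus Dunn, over the first five rows: 0.037–0.055 with one correction, 0.012–0.024 with two.
- Dunn power per comparison at δ = 5, σ = 8.2, n = 30 (one arm shifted, normal data): 0.43 with one correction, 0.28 with two.
- For the whole two-stage rule on those same data, only about 19% of trials reach the rank branch, so power per comparison moves from 0.47 to 0.44.

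**The case against.** The strongest reply is that the rule does little harm in practice. With equal group sizes its type I error is close to nominal in most scenarios. Where Kruskal–Wallis rejects with equal means, the distributions really do differ, so it is rejecting its own null correctly. The 4/4/8 case sets an exponential arm (median 5.5) against two arms with medians near 7.3, and about 2.4% of that arm would exceed the CVS-FAS maximum of 30. Item (4)(a) already supplies a mean comparison free of the gates.

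Much of this stands, and it rules out several stronger readings that a reader might infer:
- **That error rates are wrong in general.** The table does not show this; large inflation needs skew and unequal spread together.
- **That a double correction is planned.** Item (4)(a) attaches the word adjusted to the level itself, which suggests that a single 0.05/3 was meant. Only ambiguity can be asserted, and the literal reading costs power without adding false positives.
- **That the gate is reapplied for each scale and visit.** The article does not say so; it only fails to prevent it.
- **That ignoring baseline is a fault of the rank branch.** The planned one-way ANOVA does not use baseline either.

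The reply does not rescue the rule. The trial is sized on a mean difference, so equal means is the relevant null, and a sensitivity analysis does not settle which test is primary. Nor is this detail left to a fuller plan: the article states the branching rule explicitly.

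**Conclusion.** The point holds in limited form. The choice of primary test is data-driven, the quantity compared can shift between branches, and Kruskal–Wallis is not a remedy for unequal variance when the target is a difference in means. Diversion of ideal data is about 18–19% or 11%, depending on how Shapiro–Wilk is run, and nearly complete for a bounded score with a marked floor.

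Type I error for equal means stays at about 5–6% for normal data at equal group sizes and for skewed data with equal spread. Under assumed equal-mean gamma data it rises to about 6–7%, 9% and 21% as the SDs go from 4/4/5 to 4/4/8. The 21% is the extreme of that series, and the more skewed shifted-exponential case reaches 29%. None of these shapes comes from the article, so they show what could happen and do not predict it.

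The Dunn threshold is ambiguous. The power loss from 0.43 to 0.28 applies only if the text is followed literally and the rank branch is reached. The plan should be changed on these points, but they do not by themselves invalidate the trial.

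**What to change.** - Remove the Shapiro–Wilk and Levene gates from the choice of between-group test.
- Prespecify one mean-based analysis robust to unequal variance for both primary scales at all visits: a linear model with HC3 standard errors, or Welch ANOVA with Games–Howell comparisons if no covariates are used.
- Keep Kruskal–Wallis with Dunn as a sensitivity analysis.
- State one Bonferroni rule: adjusted p-values against 0.05, or raw p-values against 0.0167, not both.

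The cost is analysis-plan wording, settled before group identities are revealed, with no new data or patients. If variances are truly equal, Welch gives up a little power: omnibus 0.650 against 0.659 for ANOVA at δ = 5, SD 8.2, n = 30. With assumed SDs of 6/8.2/10 and the same shift in the first arm it gains: 0.785 against 0.716 for the two-stage rule.

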#### (3) Within-group comparisons

Paired *t*-tests (normal data) or Wilcoxon signed-rank tests (non-normal data) are used to evaluate pre-post changes.

#### (4) Sensitivity analysis

(a) Bonferroni correction: Directly applied to pairwise *t*-tests (adjusted α = 0.017).

(b) Multiple imputation: Missing values are imputed via chained equations (MICE algorithm) with 20 imputed datasets, incorporating baseline covariates and post-dropout outcomes (e.g., adverse events), which will validate results under missing-at-random assumptions. We add psychological status (baseline Hospital Anxiety and Depression Scale [HADS] scores), pain threshold (quantitative sensory testing [QST] for pressure pain tolerance at the trapezius muscle), and sociodemographic factors (age, sex, and education level) as the baseline covariates mentioned here to adjust for reliability of the subjective outcome measures.

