## Methods and design

This is a single-center, assessor- and analyst-blinded randomized controlled trial including three parallel groups, which are TNRM-UN, TNRM-TA, and UN groups. The trial will follow the guidelines of the Standards for Reporting Interventions in Clinical Trials of Acupuncture (STRICTA) (24) and the Standard Protocol Items: Recommendations for Interventional Trials (SPIRIT) (25). This study will include 6 weeks of treatment and 24 weeks of follow-up. The study period was July 2023 to December 2025. Figure 1 presents a flowchart of the trial, and Table 1 shows all schedules.

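### The plan says mood, pain and sociodemographic covariates adjust the subjective outcomes, but they enter only the imputation model and no stated comparison takes a covariate

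*Protocol article*

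**What the plan says.** All passages are in the Protocol article.

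- **Sensitivity analysis, item (b).** Missing values are imputed by chained equations "with 20 imputed datasets, incorporating baseline covariates and post-dropout outcomes (e.g., adverse events". The next sentence identifies those covariates. Mood is represented by "baseline Hospital Anxiety and Depression Scale [HADS] scores". The other items on its list are "pain threshold (quantitative sensory testing [QST] for pressure pain tolerance at the trapezius muscle), and sociodemographic factors (age, sex, and education level". The sentence also gives their purpose: they are added "as the baseline covariates mentioned here to adjust for reliability of the subjective outcome measures".
- **Between-group comparisons.** In the parametric case "one-way analysis of variance (ANOVA) is performed", with Tukey's HSD for the pairs. Otherwise a Kruskal–Wallis test is used, "followed by Dunn's test with Bonferroni-adjusted" p-values.
- **Within-group comparisons and Sensitivity analysis, item (a).** These are paired t-tests or Wilcoxon signed-rank tests, and pairwise t-tests at 0.017.
- **Methods and design.** The reader is told that "Table 1 shows all schedules". The table has rows for screening, consent, allocation, the three interventions, CVS-FAS, QBD-SAS, five vertebral artery parameters and safety. It has none for HADS or pressure pain testing.
- **Randomization and allocation concealment.** Allocation is stratified by baseline CVS-FAS score and age.

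**The concern.** Two different uses of a covariate have been run together. In an imputation model it predicts values that are missing. In the outcome model it corrects the treatment comparison for chance imbalance and reduces residual variance. The plan specifies the first and claims a benefit that could come only from the second. Even the second would not make a symptom scale more reliable as a measurement.

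The claim matters more here than it would in a blinded trial. Both primary outcomes are symptom scales. The Blinding method section says that participants are not blinded, and the Limitations section accepts that they may over-report improvement. The Introduction says that anxiety and depression may weaken the treatment response. A reader would therefore give weight to a statement that the subjective scores were adjusted for mood and pain threshold. On the analyses stated, that reassurance would be unfounded.

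The second part is a mismatch between sections. A questionnaire and a physical sensory test are relied on at baseline, but neither appears in the schedule or anywhere else in the article.

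**Working it through.** The plan gives no figure for this adjustment, so there is none to reproduce. The check sets the stated analyses side by side and then sizes the consequence.

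**1. Where a covariate can enter**

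| Stated analysis | Covariates |
|---|---|
| One-way ANOVA, Tukey | none |
| Kruskal–Wallis, Dunn | none |
| Paired t or Wilcoxon | none |
| Bonferroni pairwise t-tests | none |
| Chained-equation imputation | HADS, pressure pain, age, sex, education |

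No ANCOVA, regression or mixed model is mentioned.

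**2. How many scores imputation can touch**

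The inputs are 99 participants and 10% dropout (Sample size estimation).
- Imputed: 99 × 0.10 = 9.9, about 10.
- Observed and unchanged: 99 − 10 = 89.

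With complete data, the imputation analysis is identical to the unadjusted comparison.

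**3. What is left uncorrected**

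The inputs are 33 per arm and SD 8.2 (Sample size estimation). The correlation ρ between covariate and outcome is not in the documents and is assumed.
- Shift in the unadjusted difference per 1-SD imbalance in the covariate: ρ × 8.2.
- SD of the chance imbalance between two arms, in covariate SDs: √(2/33) = 0.246.
- Typical shift: ρ × 8.2 × 0.246.
- SD of the unadjusted difference: 8.2 × 0.246 = 2.02. After adjustment it is about 2.02 × √(1 − ρ²).

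| ρ (assumed) | Shift per 1 SD | Typical shift | SD of difference, adjusted |
|---|---|---|---|
| 0.3 | 2.5 | 0.6 | 1.93 |
| 0.5 | 4.1 | 1.0 | 1.75 |
| 0.7 | 5.7 | 1.4 | 1.44 |

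A simulation at ρ = 0.5 agrees (three arms of 33, no treatment effect, 1,500 replicates, 20 imputations where data were missing). The slope is the movement of the estimate per 1-SD imbalance.

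| Missing | Slope, impute then compare unadjusted | Slope, covariate-adjusted model | SD of difference, unadjusted | SD of difference, adjusted |
|---|---|---|---|---|
| 0% | 4.0 | −0.1 | 2.01 | 1.76 |
| 10% | 4.2 | 0.1 | 2.10 | 1.83 |

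The adjusted slopes are zero apart from simulation noise. Putting the covariate in the imputation model does not remove the dependence on imbalance. Putting it in the outcome model does.

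**4. The schedule**

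Table 1 is said to be complete, yet it also omits age (a stratification factor), sex, the 12-week symptom diaries and the monthly telephone calls described under Safety evaluation. It is therefore not a full list of what is collected. The absence of HADS and pressure pain testing from it is an inconsistency, not proof that they are not measured.

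**The case against.** The strongest reply is that the sentence is only poorly worded. Mood and pain sensitivity may predict which subjective scores go missing, so adding them to the imputation model is a legitimate use of auxiliary variables under missing at random. The article does not say which model is fitted to the 20 completed datasets, and an analysis plan that is not shown may specify one with covariates. The text sits under sensitivity analysis, and the main tests never claim to be adjusted.

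Much of this stands. The use as auxiliary variables is sound and can stay, and no sample size or alpha figure is affected. The stated purpose still fails. Nothing in the article takes a covariate outside the imputation, and on either reading the sentence needs correcting.

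A reader might go further and infer from Table 1 that HADS, pressure pain and education are never collected, so that the imputation model cannot be fitted. The documents do not support that. The text speaks of baseline HADS scores and names the muscle for the pressure test, which implies measurement. Table 1 omits other items that plainly are collected. Education is a routine demographic item that a condensed article may leave to the case report form. Even without HADS and the pressure test, chained equations could run on the remaining variables.

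**Conclusion.** The point holds as a false claim of adjustment, together with a schedule that does not match the analysis text. On the analyses stated, the named covariates can influence only the imputed scores, about 10 of 99 if dropout is 10%, and adjust none of the roughly 89 observed ones. The logic does not depend on the dropout figure, which sets only the split.

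The practical size depends on the assumed correlation. For ρ from 0.3 to 0.7, a typical chance imbalance shifts the unadjusted difference by about 0.6 to 1.4 points, against a design difference of 5. These figures use the plan's SD of 8.2 and illustrate the mechanism. They do not predict this trial's result.

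Two limits apply. The conclusion takes the comparisons in the article to be the ones applied after imputation, which is the likeliest reading but is not stated. A proper covariate-adjusted model would deal with chance imbalance and precision, but it would not remove over-reporting by participants who know their treatment.

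**What to change.** 1. **Between-group model.** Compare CVS-FAS and QBD-SAS between groups by ANCOVA with arm, the baseline score of the outcome and the stratification factors (baseline CVS-FAS and age). The plan's own 0.017 level can be applied to the three adjusted pairwise differences. All these variables are already collected, so the cost is a change of model.
2. **Sensitivity analysis, item (b).** State that HADS, pressure pain and the sociodemographic items are auxiliary imputation variables only, and remove the claim about reliability. If adjustment for them is intended and they are collected, name them as covariates of the ANCOVA before the data are analysed.
3. **Schedule.** If HADS and pressure pain testing are collected, list them in the baseline column of Table 1. If they are not, delete them and the claim, and impute from arm, baseline and earlier-visit CVS-FAS and QBD-SAS, age and sex.

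Items 2 and 3 change wording only and need no new procedure. Whether the two baseline measures exist should be checked promptly, because a pre-treatment value cannot be obtained later.

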### Safety evaluation

Acupuncture-associated adverse events (AEs) include intolerable pain, bleeding, local hematoma, and other uncomfortable feelings after acupuncture (e.g., pale face, cold, moist limbs, cold sweat, dizziness, nausea, rapid heartbeat, weak pulse, and even fainting). All AEs, which will be considered as unrelated, possibly related, or related to treatment, will be recorded and assessed by investigators on an adverse event. Investigators should record in detail the occurrence date, degree [mild, moderate, or severe (41)], duration of symptoms, and emergency measures of AEs.

Timely rescue measures will be taken for serious adverse events. Simultaneously, researchers will immediately report to the Ethics Committee, which will decide whether to withdraw the participants from the study.

To comprehensively assess delayed-onset AEs and acupuncture safety, we will take the following measures: (1) Extended follow-up duration: Participants will receive monthly telephone follow-ups for 6 months post-trial completion (up to week 48) to capture delayed-onset AEs. (2) Patient-reported outcome diaries: Participants will document daily symptoms (e.g., pain and numbness) in a standardized diary for 12 weeks post-treatment. (3) Electronic Health Record (EHR) Linkage: With participants' consent, we will access electronic health records for a 1-year post-trial to identify their hospitalizations or diagnoses potentially linked to acupuncture.

Standardized Criteria for AE Causality Assessment will adopt the following measures: (1) WHO-UMC Causality Criteria (42): (a) Certain: AE occurs post-treatment, aligns with known acupuncture effects, and resolves upon discontinuation. (b) Probable/likely: Temporal association with no confounding factors. (c) Possible: Plausible link, but alternative explanations exist. (d) Unlikely: No plausible connection to treatment. (2) Naranjo algorithm (43): A quantitative tool to score causality likelihood (scores: ≥5: “probable”; ≤ 1: “doubtful”). (3) Independent adjudication: A blinded Safety Review Board (SRB) comprising a neurologist, TCM expert, and pharmacovigilance specialist will resolve disputed cases.

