## Introduction

Cervical vertigo (CV) is a broad term encompassing dizziness caused by various cervical pathologies. In contrast, cervical spondylosis-induced vertigo refers to dizziness resulting from degenerative changes in the cervical spine, such as osteophyte formation or intervertebral disc herniation. This study focuses on the latter, as defined by the inclusion criteria. CV is associated with various symptoms such as disequilibrium, light-headedness, tinnitus, nausea, migraine, and neck pain or stiffness (1, 2). It has been reported that the estimated prevalence of CV is between 3.8% and 17.6%. Approximately 50% of patients with cervical spondylosis have vertigo symptoms (3), while 65%−66% of vertigo in elderly patients is attributed to cervical spine dysfunction (4). TCM considers that middle-aged and elderly people suffer from CV mostly due to insufficient kidney essence and deficient qi blood biochemistry. Therefore, this study is specifically concerned with CV related to qi and blood deficiency. In recent years, with the widespread use of electronic devices, the onset of CV issues has occurred at a younger age, and the risk of developing stroke and syncope is higher (5). Therefore, major academic circles are paying more attention to this disease, and it is particularly important to explore its pathogenesis, diagnostic ideas, and more effective treatment methods.

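### Two stated safety rules work against the protocol's aim of assessing delayed adverse events: the record search is filtered by suspected cause, and events starting after the last session cannot be rated certain

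*Protocol article*

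**What the plan says.** All of this stands in the Safety evaluation section of the protocol article, apart from the schedule.

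- **Investigator scale.** All AEs are to be recorded and assessed by investigators, "which will be considered as unrelated, possibly related, or related to treatment".
- **Sources for delayed events.** Three are listed: monthly telephone calls up to week 48, a daily symptom diary for 12 weeks after treatment, and EHR linkage for one year after the trial. Records are accessed "to identify their hospitalizations or diagnoses potentially linked to acupuncture".
- **Causality criteria.** A four-level list is then adopted. The top level is "Certain: AE occurs post-treatment, aligns with known acupuncture effects, and resolves upon discontinuation". The next two are "Probable/likely: Temporal association with no confounding factors" and "Possible: Plausible link, but alternative explanations exist"; the lowest is *unlikely*. A Naranjo score is added, with labels at 5 or more and at 1 or less.
- **Adjudication.** "A blinded Safety Review Board (SRB) comprising a neurologist, TCM expert, and pharmacovigilance specialist will resolve disputed cases".
- **Schedule.** Methods and design gives 6 weeks of treatment and 24 weeks of follow-up.

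**The concern.** The section's purpose is to find and judge harms that appear late. Two of its rules pull the other way.

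The EHR wording places a causal judgement in front of recording. An event that the person reading the records does not connect with acupuncture is outside the search as worded, so it would not reach the causality criteria or a comparison between arms. A randomised trial gains most from the opposite order: count every event in each arm, then judge. The Introduction says of this disease that "the risk of developing stroke and syncope is higher". Such an event is easily put down to the disease, and that attribution should be made after recording.

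The discontinuation condition closes the top level to events that start when nothing is left to discontinue. A reader who sees no late event rated *certain* could take this as reassurance, when the rule itself produces it.

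The two relatedness scales add to this. A count of related events depends on which scale is reported and on where *probable/likely* is placed, and that is the highest level a late event can reach.

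**Working it through.** No sample size, power or event count is involved, so there is no plan figure to reproduce. The check compares time windows and definitions.

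**1. Which source covers which period**

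| Source | Window | Limited by suspected cause? |
|---|---|---|
| Investigator recording (Table 1: weeks 6, 12, 24) | to week 24 | No; events judged unrelated are included |
| Diary, 12 weeks after treatment | weeks 6 to 18 (6 + 12) | No |
| Monthly calls | to week 48 | No |
| EHR linkage, 1 year after the trial | to about week 76 or 82 | Yes |

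The EHR end date depends on when the trial ends. If it ends at week 24, as Table 1 suggests, linkage runs to 24 + 52 = week 76. If the 24 weeks of follow-up start after week 6, it runs to 30 + 52 = week 82. The EHR is then the only stated source for 76 − 48 = 28 weeks, or 82 − 48 = 34 weeks. The extension study described under Limitations also stops at week 48.

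**2. Who applies the filter**

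The article does not say who reads the records or whether that person knows the arm. Acupuncturists are unblinded throughout. Blinding method and Limitations say that participants are unblinded too, although one sentence under Randomization and allocation concealment says the reverse. If the reader of the records knows the arm, the filter can differ between arms. If not, it still removes events, but without a direction tied to the arm.

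**3. What the discontinuation condition does**

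The last session is at week 6 and calls run to week 48. Time after treatment is 48 − 6 = 42 weeks, and 42/48 = 87.5% of that window. The whole EHR year is also off treatment.

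For an event that starts in this time:

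- *Certain*: needs resolution upon discontinuation. Treatment had already stopped, so read literally the condition cannot be shown.
- *Probable/likely*: needs timing and no confounding. Open.
- *Possible*: needs a plausible link. Open.
- *Unlikely*: Open.

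Three of four levels remain, and the ceiling is *probable/likely*.

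**4. The two scales side by side**

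| Investigator scale | Four-level list |
|---|---|
| related | certain |
| (no counterpart stated) | probable/likely |
| possibly related | possible |
| unrelated | unlikely |

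This pairing is only the most natural one; the article gives none. *Probable/likely* could go to related or to possibly related. If only *certain* counted as related, no event starting after week 6 could be called related. If *probable/likely* counted as well, late events could.

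**The case against.** The strongest reply is that the safety system is broader than these two sentences. All AEs are to be recorded, including those judged unrelated. Serious events go to the Ethics Committee at once. The calls and diary carry no causal filter, and potentially linked is a wide screen. Withholding the highest level where there is no evidence from stopping treatment is a defensible evidential choice. A journal article may also leave the mapping of scales and the tabulation of AEs to a fuller document.

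Much of this stands, and it rules out several stronger readings that a reader might infer.

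- *Delayed harms cannot be classified.* They can, at three of four levels.
- *Late events go unrecorded.* The causal wording attaches to the EHR item. Up to week 48 the calls can pick up the same events.
- *Stroke or syncope will be dropped.* The text does not say so. A broad reading of the filter would keep them, and the Introduction names them as risks of the disease, not as harms of acupuncture.
- *The first causality rating is unblinded.* This is not stated. Blinding method separates manipulation from evaluation and blinds the evaluators.
- *Most AEs fall in the affected window.* The 87.5% is calendar time. The AEs listed as examples are mainly reactions to needling, and no figure gives the share expected after week 6.
- *Naranjo scores of 2, 3 and 4 have no category.* The tool is cited and the parenthesis may abbreviate it. At most this is a clarification.
- *The Safety Review Board must see every serious or severe event.* A board that settles disputes is a coherent arrangement, and wider referral is a preference.

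What the reply does not remove is the wording of the two rules. Both are stated, not omitted. After week 48 no unfiltered source is named.

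**Conclusion.** The point holds in limited form. The EHR rule filters events by suspected cause before they are recorded, in the only source named for roughly 28 to 34 weeks after the last call. The definition of *certain* caps events starting after week 6 at *probable/likely*. The two unreconciled scales are a lesser fault that makes the cap harder to interpret.

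This rests on three assumptions: the EHR sentence means what it says, *resolves upon discontinuation* is read literally, and the trial ends at week 24 or week 30. The number of events affected cannot be estimated from the document. No efficacy result, sample size or error rate depends on it. It is worth correcting because safety is a stated objective and the correction is cheap.

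**What to change.** 1. **EHR.** Extract all hospitalisations and new diagnoses over the linked year, for every consenting participant in all three arms. Record them, then judge causality blind to group. Since all arms receive acupuncture, the comparison shows an excess of one regimen over another, not the risk against no treatment. Cost: a somewhat longer extract from records already linked, and more events to review.
2. **Discontinuation criterion.** State that it is not applicable to events starting after the last session. Report those events as their own group, and say that the absence of *certain* ratings there is not evidence of no link. This does not let late events reach the top level on less evidence. Cost: two sentences and one table row.
3. **Relatedness scale.** Name one governing scale and state how the other maps to it, in particular where *probable/likely* falls. Cost: wording only.

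Optional: give the label for Naranjo scores 2 to 4 and the role of that score, and say what makes a case disputed for the Safety Review Board.
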